### Plans to promote participant retention and complete follow-up {18b}

The process evaluation team will identify and address the key challenges to retention from the perspective of overall acceptability. Participant flow at sites, recruitment consultations, and interviews with patients and site staff will be analysed. Potential solutions in the form of action plans will be developed, implemented and evaluated on a rolling case basis.

Participants are sent up to two reminders to complete the follow-up questionnaires. First attempts and first reminders are emailed, posted or texted to participants, in accordance with their preference. The final reminder is attempted by telephone. If there is no response by telephone, the final reminder is sent by post. If questionnaires are returned as non-deliverable, attempts will be made by site staff or the trial office to trace the participant. Questionnaires are administered to all participants who were randomised in the trial, regardless of whether they had the surgery they were allocated, unless they have withdrawn from questionnaire follow-up.

Preferable measurement windows for the key eGFR measurements are specified within the protocol. An out of window measurement is preferable to no measurement at any timepoint. Therefore, all eGFR tests post-randomisation up to 24 months post-intervention, including out of window measurements, are collected and will be incorporated into the analysis.

All other outcomes are collected from the participant’s medical records, unless the participant has specifically withdrawn consent for collection of outcome data.

Participants are followed up for trial outcomes unless they have withdrawn from all aspects of the trial. All data collected up to the point of complete withdrawal from the trial is retained and used in the analysis. Participants for whom any outcome data are available are included in an intention to treat analysis.

### Data management {19}

Outcome data is either entered directly into the trial database (hosted by CHaRT, University of Aberdeen) or completed as a hardcopy and then entered onto the trial database by the local research team. Postal questionnaires are entered into the trial database by the trial office. The trial office works closely with local research teams to ensure the data is as complete and accurate as possible. For the first participants recruited at each site, the trial office reviews hardcopy case report forms and baseline participant questionnaires, entered by the local research team into the trial database, to check accuracy of data input. The trial database includes automated range and validation checks. Regular data accuracy spot checks are completed on questionnaires entered into the trial database by the trial office. All consent forms are checked for errors.

### Confidentiality {27}

Data collected during the course of the research is kept strictly confidential and accessed only by members of the trial team. Data may be looked at by individuals from the Sponsor organisation or NHS sites where it is relevant to the participant taking part in this trial. Personal data is retained only as long as is necessary for the purpose for which it is processed. The chief investigator and trial staff involved with this project will comply with the requirements of the General Data Protection Regulations (GDPR) and the Data Protection Act 2018. Trial staff based in Scotland will also adhere to the current version of the NHS Scotland Code of Practice on Protecting Patient Confidentiality. Access to collated participant data is restricted. All data input/access is via secure Virtual Private Network and/or secure website. Limited access measures, robust authentication and pseudonymisation are used to protect participant data. Published results will not contain any personal data that could allow identification of individual participants.

### Plans for collection, laboratory evaluation and storage of biological specimens for genetic or molecular analysis in this trial/future use {33}

We plan to seek separate funding to establish a well-characterised cohort of patient tissue including clinical data, urine, blood and tumour specimens which will allow future measures of biomarker for detection, surveillance and prognosis, and inform best treatment strategies.

## Statistical methods

### Statistical methods for primary and secondary outcomes {20a}

All statistical analyses will be pre-specified in a comprehensive Statistical Analysis Plan which will be agreed with trial steering committee (TSC) and data monitoring committee (DMC).

All analyses will be based on the intention-to-treat principle. The primary outcome, difference in kidney function decline, will be analysed using a mixed effects repeated measures generalised linear model that includes a random effect for participant and centre, with fixed effects for treatment, nominal time points, and design covariates and adjusted for baseline eGFR. Treatment effect estimates will come from the time-by-treatment interactions and the primary focus is on the 2-year timepoint. A second analysis of this outcome will use a latent growth model on kidney function measures at all time points to explore the trajectory of decline between groups. The CCI at 90 days will be compared between groups, initially using linear regression, using the bounds of the 95% CI around the difference, to test non-inferiority. However, there is potential for the CCI distribution to violate the assumptions of linear regression—if that occurs, we will use a more appropriate analysis method, e.g. beta regression on CCI scores transformed to the (0,1) interval. Positive surgical margins will be analysed as a binary outcome using logistic regression model including a random effect for centre, with fixed effects for treatment and design covariates. Treatment effects for positive surgical margins will be summarised using absolute percent differences.

The HRQoL outcomes will be analysed in two ways—an analysis of the area under curve and a repeated measures analysis using a time-by-treatment-interaction. Other secondary outcomes will be analysed in a similar way with generalised linear models appropriate for the distribution of the outcome. Treatment effects will be summarised with treatment estimates and 95% confidence intervals.

The trial includes a within trial and model based economic evaluation. Full details of the health economics analyses will be set out in the Health Economics Analysis Plan (HEAP).

The within trial economic evaluation will be conducted on an intention to treat principle. Results will be presented as a cost-consequence analysis and a cost-utility analysis from the NHS and personal social services perspective for the 24-month trial follow-up. A broader perspective incorporating costs to patients and their families will form part of sensitivity analysis. Our base case analysis will adopt standard purchasing approaches used in existing economic evaluations [54], but we will also explore alternative equipment costing assumption. The unit costs of NHS and personal social services resource use will be estimated from trial specific estimates and routine data sources [55, 56]. Unit costs will be combined with information on the use of services to estimate a cost for each participant and a mean cost for each intervention arm.

The relative changes in HRQoL captured by the SF-36 will be converted to SF-6D scores [57] and QALYs estimated using the area under the curve approach [58]. As part of sensitivity analysis, we will map the EORTC QLQ-C30 (administered at the same time points as the SF-36) on to the EQ-5D valuation set and these used to estimate QALYs.

An appropriate regression model will be fitted to estimate marginal costs and QALY gains, controlling for baseline covariates. Data will be presented as point estimates and bootstrapping techniques characterise imprecision [59]. The results will be presented as cost and QALY plots and as cost-effectiveness acceptability curves [60]. The cost-consequence analysis will be presented as a balance sheet to illustrate the trade-offs between different health outcomes.

An economic decision model (e.g. a microsimulation model) will extrapolate costs and outcomes over the lifetime of the patient. The model will be used to produce estimates of costs and QALYs. Cost-effectiveness will be reported as incremental cost per QALY gained at both 24 months and over the patient’s lifetime.

For both the within trial and the model-based analyses, costs and effects occurring after 1-year will be discounted at the recommended rates, currently 3.5% per annum.

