Currently, there are no ongoing RCTs of PN vs RN for surgical treatment of smaller renal tumours. Previous evidence syntheses have relied predominantly on retrospective cohort data [9, 10]. A Cochrane review identified the only randomised controlled trial (RCT) comparing PN and RN for small RCCs (< 5 cm) [11]. This RCT did not meet its pre-planned accrual targets and the technical approaches to PN were still being refined. A 21% crossover occurred, mainly PN to RN due to perceived technical challenges, affecting the intention-to-treat analysis [12]. In terms of overall survival, non-inferiority of PN was not demonstrated [13]. Given the absence of high-quality evidence, the authors of the Cochrane review recommended a methodologically rigorous study to assess the potential benefits and harms of PN, whilst accounting for baseline renal function, tumour size and patient age [11]. Technical advances with minimally invasive robotic PN have rapidly progressed and the clinical climate is now receptive to the conduct of an RCT. More recently, < 5% of procedures were reported to convert from PN to RN [14–16].

Following both PN and RN, renal function initially falls but compensations can occur with within the first 9 months after surgery and stabilises beyond the first 12–18 months [3, 17]. In Van Poppel et al., mean estimated glomerular filtration rate (eGFR) stabilised at 12 months at 52.7 ml/min/1.72m^2^ with RN and 66.8 ml/min/1.72m^2^ with PN [12]. Reductions of renal function to these levels are associated with a 5-year risk of (i) ESKD approaching 1% in both groups [3] and (ii) cardiovascular events of 9.9% and 15.6%, for PN and RN respectively [18, 19]. Although not reproduced in the Van Poppel study, these risks of cardiovascular events are consistent with the 40% increase shown by comparing eGFR > 60 vs GFR = 45–59 ml/min/1.73m^2^ in a longitudinal cohort study that is a seminal paper in the nephology field [20].

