### Sample size {14}

Our sample size is based on the primary outcome of kidney function, and is also adequate for a 90% power non-inferiority test on the CCI. We will have precision to describe positive surgical margins and quality of life:(i)For kidney function, we have used the width of the confidence interval between the groups in eGFR at 2 years: We estimate from systematic reviews that the absolute difference between PN and RN groups in arresting kidney function decline from baseline will be an eGFR of at least 10 ml/min/1.73m^2^, with a standard deviation of 16 [9, 19, 44]. This is a minimal clinically important difference informing international guideline recommendations for PN [45–48]. Based on the only randomised data available for PN vs RN, we predict a difference of at least 15 ml/min/1.73m^2^ at 2 years [3, 12]. As we require the confidence interval around the estimated difference to rule out a minimal clinically important difference of 10 ml/min/1.73m^2^, we have used a confidence interval of width 7. To be 90% sure our two-sided 95% confidence interval is at most 7, requires outcome data on 178 participants in each arm, or 356 participants in total. We will gain extra precision by using participants’ baseline eGFR in analysis.

We have inflated the sample size to account for 15% of potential attrition over 2 years to 420 randomised participants in total.

(ii)We require CCI outcome data on 380 procedures for 90% power to rule out a 4-point non-inferiority margin (i.e. we would tolerate up to 4 points higher CCI in the PN group) using the upper bound from a one-sided 97.5% confidence interval around the difference in means between the groups. The 4-point margin was derived using expert opinion and patient and public involvement on a non-inferiority margin for major complications, and from data on a minimally important difference in the CCI [32].(iii)With 420 procedures, we will have adequate precision to describe rates of positive surgical margin over a range of scenarios. Positive surgical margin rates up to 5% may be expected, with only < 1% requiring re-treatment [49].(iv)Our sample size also gives adequate power/precision to compare quality of life (expressed as area under curve analysis between randomisation and 24 months), with approximately 90% power to detect a third of standard deviation.

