## Assignment of interventions: allocation

### Sequence generation {16a}

Participants are randomly allocated using a remote central, computer-generated randomisation system accessed on the trial website (developed and administered by the Centre for Healthcare Randomised Trials (CHaRT), University of Aberdeen). The allocation algorithm uses centre, pre-operative eGFR (45–59; ≥ 60), tumour size (T1a; T1b), and pre-randomisation biopsy (yes; no) as minimisation covariates to allocate to PN or RN.

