**Assessments:**									
Baseline characteristics	X								
Renal function: eGFR^a^	X		X	X		X	X		X
Quality of life: EORTC QLQ-C-30, SF-36	X		X	X	X	X	X	X	X
Participant cost questionnaire	X					X	X	X	X
Participant time and travel							X		
Comprehensive Complications Index					X				
Quality of recovery: QoR-15			X	X	X				
Late complications						X	X	X	X
Cardiovascular events									X
Recurrence^b^									X
Further treatment									X
Surgical details & resource use		X							
Pathology & positive surgical margins		X							
Patient acceptability					X				

*eGFR* estimated glomerular filtration rate, *EORTC QLQ-C30* European Organisation for Research and Treatment of Cancer Quality of Life Questionnaire Core 30,
*QoR-15* 15-Item quality of recovery scale, *R0* date of randomization, *SF-36* 36-Item Short Form Survey Instrument, *S0* date of surgery

^a^There are preferable measurement windows for eGFR at key timepoints: 1 week post-surgery (within 1 week of surgery); 1 month post-surgery (± 1 week); 6 and 12 months post-randomisation (± 1 month); 24 month post-randomisation (± 3 months). All eGFR tests, including out of window observations, are recorded

^b^This outcome is not collected in participants who do not have confirmed renal cell carcinoma (RCC)

At baseline, the local research team captures baseline demographic and clinical information, including baseline renal function (eGFR) and tumour size and surgeon assigned location parameters (for PADUA classification [21]). Participants are asked to complete a baseline questionnaire prior to randomisation. During follow-up, the local research team collects outcomes from participant medical notes.

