### Methods for additional analyses (e.g. subgroup analyses) {20b}

Pre-planned subgroup analysis includes pre-operative eGFR, any comorbidity (diabetes affects 20%, hypertension affects 60% and cardiovascular disease affects 20%) [61], smoking status, age and size of tumour.

Pre-operative renal biopsy is not a standard of care across the UK and is not mandated for recruitment into the trial. Participants found to have a non-cancerous mass will remain in the trial. The effect of this will be explored by a post hoc sub-group analysis if the numbers in both confirmed RCC and no RCC are sufficient. If one of the groups is too small for a sub-group analysis, a sensitivity analysis will be undertaken.

For the economic evaluation, sub-group and sensitivity analyses will be replicated where these are relevant to the estimation of costs and QALYs. Deterministic sensitivity analyses will be combined with the trial-based stochastic or model-based probabilistic analyses to explore other forms of uncertainty (e.g. different cost assumption, inclusion of participant costs, QALYs based on EORTC QLQ-C30 responses).

For the process evaluation, analysis of patient recruitment pathways using the Screened, Eligible, Approached, Randomised (SEAR) framework will be applied to identify and assess areas of complexity and protocol compliance [53]. The transcripts of the recruitment consultations will be analysed using content and thematic analysis, focusing on modifiable aspects of recruitment consultations. A novel mixed-methods approach combining consultation timings (time spent explaining aspects of the RCT) and qualitative interpretation of the conversation (quanti-qualitative appointment timing) may be used for the purpose of analysis as appropriate. Sample characteristic information will be presented using frequencies. Data collection and analysis of patient and site staff interviews will be informed by the Theoretical Domains Framework and/or the Theoretical Framework of Acceptability, which has been applied in existing studies exploring trial feasibility in other contexts [62].

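### The stated primary eGFR model omits age, which is already collected; adding it as a prespecified covariate would be a small, free gain in precision

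*Protocol article*

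**What the plan says.** The section on statistical methods for primary and secondary outcomes {20a} leaves full detail to a statistical analysis plan. It also describes the primary model: a mixed-effects repeated-measures model with random effects for participant and centre, "with fixed effects for treatment, nominal time points, and design covariates and adjusted for baseline eGFR".

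Sequence generation {16a} lists the allocation factors: centre, pre-operative eGFR in two classes, "tumour size (T1a; T1b), and pre-randomisation biopsy (yes; no) as minimisation covariates". I take these to be the design covariates of {20a}.

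The background {6a} reports that the authors of a Cochrane review called for a rigorous study of the benefits and harms of partial nephrectomy "whilst accounting for baseline renal function, tumour size and patient age".

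Age appears as an analysis variable only in {20b}, among the planned subgroup factors: "smoking status, age and size of tumour". For tumour size, the text under Table 1 in {18a} says that sites record "tumour size and surgeon assigned location parameters" at baseline, so a measure finer than two classes appears to be available.

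**The concern.** Of the three variables named in the cited recommendation, baseline renal function is adjusted for directly, tumour size enters as two classes, and age is neither balanced by minimisation nor adjusted for in the primary model. Listing age as a subgroup factor does not adjust the primary estimate.

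Precision matters here because the sample size section {14} is built on confidence interval width: the interval for the 2-year difference has to be narrow enough to rule out 10 ml/min/1.73m². If age predicts 2-year eGFR beyond baseline eGFR, leaving it out widens that interval a little, and any chance age difference between the arms stays in the point estimate. An analysis plan that followed {20a} to the letter would carry the omission forward.

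**Working it through.** **Inputs from the documents.** The sample size section {14} gives "eGFR of at least 10 ml/min/1.73m^2^, with a standard deviation of 16", a two-sided 95% interval of width at most 7 with 90% assurance, 178 per arm (356 in total), 15% attrition, 420 randomised, and a predicted difference of at least 15. Allocation is 1:1.

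**Assumption not in the documents.** r, the partial correlation of age (or continuous tumour size) with 2-year eGFR once baseline eGFR and the design covariates are in the model. Range used: 0.1 to 0.3, with 0.5 as an extreme.

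**Step 1: reproduce the plan's figure.** Find the smallest n per arm with P(2 × t(0.975, 2n−2) × s × √(2/n) ≤ 7) ≥ 0.90, where s² is distributed as 16² × χ²(2n−2)/(2n−2).
- n = 177: assurance 0.894.
- n = 178: assurance 0.908. The stated 178 reproduces exactly.
- 356 / 0.85 = 418.8, so 419 against the stated 420, a matter of rounding.
- Width at n = 178 and s = 16: 6.67. The target of 7 is met with no covariate.

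**Step 2: effect of adding age.** Residual SD = 16 × √(1 − r²), so the width is multiplied by √(1 − r²).

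| r | Residual SD | Width at 178 per arm | Narrowing | n per arm for 90% assurance |
|---|---|---|---|---|
| 0 | 16.00 | 6.67 | none | 178 |
| 0.1 | 15.92 | 6.64 | 0.5% | 176 |
| 0.2 | 15.68 | 6.54 | 2.0% | 171 |
| 0.3 | 15.26 | 6.36 | 4.6% | 163 |
| 0.5 (extreme) | 13.86 | 5.78 | 13.4% | 136 |

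The percentage narrowing is the same whatever baseline eGFR has already removed from the SD; only the absolute widths would be smaller. For r from 0.1 to 0.3, each confidence bound moves by half the change in width: (6.67 − 6.64)/2 ≈ 0.02 to (6.67 − 6.36)/2 ≈ 0.16 ml/min/1.73m².

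**Step 3: chance that the lower bound exceeds 10.** Standard error = 16 × √(2/178) = 1.70. If the true difference is 15, the chance is Φ(5/1.70 − 1.96), about 84%. With age at r = 0.2 the standard error is 1.66 and the chance about 85%; at r = 0.3 they are 1.62 and about 87%.

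**Step 4: chance age imbalance.** With 178 per arm, the 95% range of the standardised age difference is ±1.96 × √(2/178) = ±0.21 SD. The shift in the eGFR difference if age is left out is r × 16 × 0.21: about 0.3, 0.7 and 1.0 ml/min/1.73m² at r = 0.1, 0.2 and 0.3. These are upper-end values, because baseline adjustment makes the SD smaller than 16.

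**Step 5: continuous tumour size instead of T1a/T1b.** If the 4 cm cut acts like a median split of a normal variable, two classes keep 2/π of the variable's R². The width ratio is √((1 − r²)/(1 − 2r²/π)), which gives 0.2%, 0.7% and 1.7% narrowing at r = 0.1, 0.2 and 0.3. A more uneven split would keep less, but the gain cannot exceed what the whole covariate brings in Step 2.

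**The case against.** The best reply is that nothing here is wrong. The article defers to an analysis plan that is not shown, and extra prognostic covariates are routinely settled there. The stated model adjusts for the minimisation factors and the baseline value of the outcome, and it is valid as it stands. That reply holds, and it sets the low priority. It does not remove the point, because {20a} gives a definite covariate list without age instead of staying silent.

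Several stronger readings are tempting and are not supported.
- **That the protocol breaks its own commitment.** The recommendation belongs to the review authors and concerns a future study. It does not say that accounting for a variable means a covariate in the primary model, and the trial does use age as a subgroup factor.
- **That the primary estimate is biased.** Randomisation balances age in expectation, and the confidence interval already allows for chance imbalance.
- **That the trial is underpowered or short of its target width.** Step 1 shows otherwise. With an observed difference of 15, the lower bound is about 15 − 3.3 = 11.7 without age.
- **That the gain is worth dozens of participants.** That needs figures the documents do not contain. An age SD of 11 years, a slope of 0.4 ml/min per year and a residual SD of 12 give R² = (0.4 × 11)²/12² = 0.134 and a 7% narrower interval, but this is the extreme corner of a set of assumptions. The documents also do not say that age governs how well the remaining kidney compensates.
- **That baseline eGFR is wrongly given one slope across all visits.** The text does not say whether that term interacts with time.
- **That the model for the Comprehensive Complication Index also needs age.** Nothing in the documents supports this.

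**Conclusion.** The point stands as a modest efficiency gain. Age is absent from both the minimisation and the stated primary model, although it is to hand and is named in the recommendation that the rationale cites. For an assumed partial correlation of 0.1 to 0.3, adjustment would narrow the interval by about 0.5 to 5% and remove a chance shift of at most about 1 ml/min/1.73m². The direction is safe if age has any prognostic value after baseline eGFR; the size rests wholly on that assumed correlation. Continuous tumour size is worth less, under 2% if the T1a/T1b cut behaves like a median split. Low priority.

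**What to change.** Add age in years, as a continuous fixed covariate, to the primary eGFR model, and record this in the analysis plan before any outcome data are analysed by arm. Adding it later, after seeing an imbalance, would be a data-driven choice. Tumour size in continuous form may be added beside the T1a/T1b factor if the team wishes.

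The cost is one line of text and one degree of freedom per covariate. Age is already required for the planned subgroup analysis and tumour size is already recorded, so recruitment, randomisation and follow-up are unaffected. There is time: the single effectiveness analysis comes after follow-up ends, now expected in September 2028.

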Most complications for both PN and RN occur acutely in the peri-operative period, such as bleeding and urine leaks. The main determinants of perioperative complications relate to the anatomy of the tumour—captured and categorised by a number of renal morphometric scoring systems, such as the Preoperative Aspects and Dimensions Used for Anatomic (PADUA) classification and Radius Exophytic/endophytic Nearness Anterior/posterior Location (RENAL) nephrometry score [21, 22]. The main variables determining complexity and risk of complication are size, higher-risk endophytic or favourable exophytic growth pattern, and higher-risk hilar locations next to main feeding vessels versus peripheral locations [8, 23]. Work from our group shows that depending on surgical complexity, moderate to severe complications (Clavien-Dindo 3 or higher) are seen in 4–11% of PN compared with just 2–3% in RN treated by robotic approaches [22]. Acceptable thresholds of complication are not well described, and most studies fail to provide information about the cumulative severity of complications, or inform only on the most severe event, ignoring events of lesser severity.

To define the key parameters for our trial, we undertook detailed surveys and focus groups with key stakeholders (patients, urologists and nephrologists). Patients with lived experience of RN or PN (*n* = 24) agreed that a clinical trial is urgently required to determine which treatment is superior in terms of relative benefits and harms for intermediate sized tumours. They shared that main drivers in decision-making were an intuitive and strong desire to maintain kidney function and avoidance of harm by prioritising being cured of cancer and returning to normal activities as soon as possible. The main drivers for urological surgeons (*n* = 110) considering PN vs RN are potential harms (related to the anatomy of the tumour). Otherwise, there was a strong conviction to save renal function where possible. In cases of T1b tumours (with the solitary exception of hilar endophytic T1b cases) and endophytic hilar T1a tumours, there was equipoise from urological surgeons regarding the best approach. Nephrologists (*n* = 32) chose an eGFR difference of at least 10 ml/min/1.72m^2^ between PN and RN as being a minimal clinically important difference and, triangulating these findings with those from the urologists and patients, informed the design of our trial and its co-primary outcomes.

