## Trial design {8}

PARTIAL is a pragmatic patient-randomised controlled, parallel group superiority trial, with an embedded economic evaluation comparing PN and RN for patients with suspected or confirmed renal cell carcinoma (RCC). Patients are approached to participate following informed decision-making and electing for a surgical approach. Patients are allocated to PN or RN in a 1:1 ratio. Trial treatments follow routine clinical management protocols.

The trial includes an internal pilot phase with an embedded mixed-methods process evaluation which aims to identify significant challenges relating to design or conduct that can be addressed and modified before progression to full trial.

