### Outcomes {12}

Co-primary outcome measures:
(i)Gains in preserving renal function as measured by eGFR (using the Chronic Kidney Disease Epidemiology Collaboration (CKD-EPI) 2009 formula without the race coefficient as recommended by the National institute for Health and Care Excellence, the UK Kidney Association and European Federation of Clinical Chemistry and Laboratory Medicine [29–31]). The adjusted mean difference between the eGFR score in the PN and RN groups will be analysed to determine if PN results in better maintenance of eGFR compared with RN. This co-primary outcome timepoint is at 2 years post-randomisation, and it will be possible to present effect sizes at all follow-up points using a repeated measures model.(ii)Harms captured by Comprehensive Complication Index (CCI). The CCI is validated in renal surgery [32, 33] and based on the Clavien-Dindo classification (reporting on the most severe event) and is calculated as the sum of all surgical complications that are weighted for their severity [34]. Ideally, the CCI will be analysed as an adjusted mean difference between the PN and RN groups, but the distribution or heteroscedasticity may require a different analysis. This co-primary outcome timepoint is reported at 3 months post-intervention (i.e., collecting events over the peri-operative period after skin closure for the index procedure to three months after surgery).

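### The CCI non-inferiority margin is 4 points on the difference in means, but the permitted fallback analysis, with beta regression as its only named example, is not tied to that scale

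*Protocol article*

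**What the plan says.** Sample size {14}, item (ii), defines the harms test: "We require CCI outcome data on 380 procedures for 90% power to rule out a 4-point non-inferiority margin", "using the upper bound from a one-sided 97.5% confidence interval around the difference in means between the groups". The direction is explicit: "we would tolerate up to 4 points higher CCI in the PN group". The criterion is therefore in raw CCI points, partial nephrectomy (PN) minus RN, on a difference in means.

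Statistical methods {20a} starts with linear regression and compares the confidence bounds with the margin. If the CCI distribution breaks that model's assumptions, "we will use a more appropriate analysis method, e.g. beta regression on CCI scores transformed to the (0,1) interval". Outcomes {12} prefers an adjusted mean difference, "but the distribution or heteroscedasticity may require a different analysis".

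The article does not restate the 4-point margin for a fallback model, ask for that model's result as a mean difference in points, or say how zero scores are moved into the open interval. It does say that all analyses will be pre-specified in a statistical analysis plan, which is not shown.

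**The concern.** The CCI is a severity-weighted sum over complications, so everyone without a complication scores exactly zero. Beta regression is undefined at zero. Any transformation into (0,1) must give those patients an artificial small value, and the fit then depends heavily on it. The usual coefficient is on the logit scale, where no 4-point margin exists. Converting it back to points gives a mean difference that can be trusted only if the beta model describes the data, and a spike at zero is one likely reason for leaving linear regression in the first place.

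At stake is the conclusion on a co-primary outcome that exists to detect excess harm from PN. An estimate pulled towards zero makes non-inferiority of PN easier to declare.

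**Working it through.** **1. The stated sample size.** Inputs from Sample size {14} and Trial design {8}: margin 4, one-sided 2.5%, power 90%, 1:1 allocation, 380 procedures. The SD is not stated, so it is solved for.

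n per arm = 2 × (1.960 + 1.282)² × SD² / 4². With SD 12: 2 × 10.51 × 144 / 16 = 189.1, rounded up to 190 per arm, or 380. Solving for exactly 190 gives SD 12.03. This is a consistency check only: SD 11 would need 318 and SD 13 would need 444. The stated 380 is not shown to be wrong.

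**2. Why the beta fit can miss a mean difference.** With a logit link, one precision φ and two arms, maximum likelihood sets the mean of logit(y) in arm j equal to ψ(μ_j φ) − ψ((1 − μ_j)φ), where ψ is the digamma function. The fit therefore matches the average logit in each arm, not the average score.

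Under the common transformation y' = (y(N − 1) + 0.5)/N, with y the CCI divided by 100 and N = 380, a zero becomes 0.5/380 = 0.0013, with logit −6.6. A score of 16 has logit ln(0.16/0.84) = −1.7, and a score of 32 has ln(0.32/0.68) = −0.8. Going from 0 to 16 moves the logit by about 5. Going from 16 to 32 moves it by only 0.9, although both steps are 16 points on the scale of the margin. Differences in severity nearly vanish.

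**3. False non-inferiority at a true difference of 4.** The simulation used 190 per arm and 1,000 trials per row. Beta regression had common precision and was converted back to points with a delta-method 95% interval. The comparator was the unadjusted mean difference with an unequal-variance 95% interval. Shares of zeros and the non-zero score distributions are assumptions.

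| How PN differs | RN zeros | Beta estimate (points) | False NI, beta | False NI, raw means |
|---|---|---|---|---|
| Frequency | 80% | 1.68 | 99% | 1.9% |
| Frequency | 70% | 2.26 | 70% | 2.0% |
| Frequency | 60% | 3.03 | 19% | 2.0% |
| Frequency | 50% | 3.94 | 3% | 2.3% |
| Severity only | 50–75% | 0.39–0.65 | 98–100% | 2.3–3.0% |
| Both | 60–80% | 0.99–1.75 | 84–100% | 1.8–2.9% |

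**4. Sensitivity.**
- Sandwich standard errors did not help: 100%, 84%, 27% and 4% in the four frequency rows.
- Gamma-distributed non-zero scores, RN zeros 60–80%: 20–98% (frequency) and 98–100% (severity). The raw mean difference gave 2.1–4.3%.
- Five ways of moving the zeros, frequency scenario: 94–100% at 80% zeros, 57–77% at 70%, 13–24% at 60%.
- Mean non-zero score of 25, RN complication share 10, 15, 25 and 40%: 100%, 100%, 84% and 16%.
- A further set with the RN complication share rising from 10% to 50%: 100% falling to 5% for a frequency difference, and 54–100% for severity only. Raw means gave about 0.3–3%.
- Arm-specific precision: 12%, 12%, 7% and 3% at RN complication shares of 10, 15, 25 and 40%. Repeat runs gave 10%, 10%, 3% and 3.5% at the same shares, and about 1–8% in the further set.
- RN complication share 60%, frequency difference, common precision: the estimate rises to 4.5–4.75 points, so the bias now works against PN.
- Data drawn from a true beta distribution and then transformed: estimates 3.3–3.6, false non-inferiority 5–9%.

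**The case against.** Several stronger readings are tempting, and the article does not support them.

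*That the trial is committed to beta regression.* It is not. Linear regression comes first, and beta regression is given only as an example. The unseen analysis plan may choose another model, a different precision structure or a standardised mean difference. The article already reports a logistic model for surgical margins as an absolute percentage difference, so its authors do convert from the logit scale elsewhere.

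*That the article's own rates show most scores will be zero, making the switch close to automatic.* They do not. The figure given is "moderate to severe complications (Clavien-Dindo 3 or higher) are seen in 4–11% of PN compared with just 2–3% in RN treated by robotic approaches". The CCI also counts lesser complications, and no rate for any complication is given. With about 190 per arm, a statistician could reasonably keep the mean difference despite skewness, and the article does not say that non-normality alone forces a change.

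*That beta regression always favours PN, or always fails badly.* The very high error rates need both many zeros and common precision. With arm-specific precision the problem is modest, and with a frequency difference it fades or reverses when half or more of RN patients have a complication.

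What remains is not missing detail. The article fixes the margin on one scale, permits a change of method for the same co-primary test, and names as its only example a method whose standard form can fail that margin.

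**Conclusion.** The point holds in a conditional form. The margin and the permitted fallback are not tied together, and the one method named can give a wrong non-inferiority conclusion. If 10–40% of RN patients have a complication, common-precision beta regression gives false non-inferiority of roughly 16–100% under a frequency difference. Under a severity-only difference it is about 50–100%, against a nominal 2.5%. Arm-specific precision brings this to about 1–12%. The raw mean difference with an unequal-variance interval stays at or below about 4% in every scenario tried.

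These figures rest on assumed shares of zeros, assumed non-zero scores and an unadjusted two-arm comparison. They show what can happen, not what will. They do not show that the planned number of participants is wrong.

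**What to change.** In Statistical methods {20a}, and in the analysis plan, state that the non-inferiority test is always made on the adjusted difference in mean CCI points (PN minus RN), whatever the observed distribution. Use a heteroscedasticity-robust or bootstrap 95% confidence interval and compare its upper limit with 4. Say that beta, two-part or rank-based models may be reported as supportive descriptions but do not decide the margin test. Align the wording on possible alternative analyses in Outcomes {12}.

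The cost is a sentence or two. No new data are needed, and the sample size does not change: with the back-solved SD of 12, 380 procedures still give 90.1% power. Trial status puts the last follow-up in September 2028, so the change can be made well before analysis.
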